# The Effects of Resistance Exercise With Blood Flow Restriction on Flow-Mediated Dilation and Arterial Stiffness in Elderly People With Low Gait Speed: Protocol for a Randomized Controlled Trial

**DOI:** 10.2196/14691

**Published:** 2019-11-01

**Keywords:** blood flow restriction, arterial stiffness, elderly people

## Abstract

**Background:**

During aging, a significant loss of muscle mass, strength, and power is associated with a decline in daily functional capacities. Traditionally, resistance training is prescribed to prevent or reverse the skeletal muscle weakness, but the required training intensity may be too demanding for older people with poor physical performance. Resistance exercise with blood flow moderation (KAATSU training), originally developed in Japan, combines resistance exercise with blood flow restriction. It has been reported that KAATSU training enhances muscle hypertrophy in many populations. However, few studies have evaluated the effects of resistance exercises with blood flow restriction in elderly people and how this affects vascular structure and function.

**Objective:**

The aim of this study was to evaluate (1) the acute and chronic effects of resistance exercise with blood flow restriction on vascular health in elderly people with low gait speed and (2) whether low-load resistance training with blood flow restriction elicits similar strength and gait speed gains to those elicited by conventional resistance training without blood flow restriction.

**Methods:**

This is an ongoing randomized controlled trial in elderly people with low gait speed. Overall, two study arms of 13 participants each perform resistance exercise with and without blood flow restriction. The 2 groups are as follows: the control group will perform conventional resistance exercise (60% of 1 repetition maximum) and the KAATSU group will perform the low-load resistance exercise with blood flow restriction (20% of 1 repetition maximum) for 12 weeks. Pulse wave velocity, venous occlusion plethysmography, and flow-mediated dilation are used to assess arterial stiffness, muscle blood flow, and endothelial function, respectively. The secondary outcomes are gait speed, strength, and quality of life. All measures will be performed before and after the training program.

**Results:**

This research study is in progress. Recruitment has started, and data collection is expected to finish in August 2020.

**Conclusions:**

The findings of this study will have important implications for the rehabilitation of elderly people.

**Trial Registration:**

ClinicalTrials.gov NCT03272737; https://clinicaltrials.gov/ct2/show/NCT03272737

**International Registered Report Identifier (IRRID):**

DERR1-10.2196/14691

## Introduction

### Background

According to the World Health Organization, many countries, including China, Thailand, and Brazil, will see an increase in the percentage of the population over 65 years, from 7% in 2000 to 14% in the 2030s [1].

This increase in the proportion of older people represents a huge challenge for health care as aging is accompanied by decrements in cardiovascular function, skeletal muscle weakness, and changes in blood coagulation, all of which have a negative impact on the functional capacity of the elderly person [2,3].

Therefore, strategies that can prevent, minimize, or even reverse these effects of aging are imperative to maintain mobility and the ability to perform activities of daily living that are fundamental for the autonomy of elderly people [4].

### Senescence and Skeletal Muscle System

One of the major factors contributing to the age-related muscle wasting is disuse; however, even master athletes show aging-related muscle wasting and weakness, suggesting that other factors, such as an inherent aging process, must also contribute [5].

Elderly people with muscle weakness have 2.6 times higher risk of severe mobility limitation, 4.6 times higher risk of low gait speed, and 2.1 times higher risk of mortality compared with elderly people without muscle weakness [6].

### Senescence and the Cardiovascular System

Progressive loss of cardiomyocytes, reduction of the β_1_-adrenergic response, and degenerative alterations in the sinus node are all hallmarks of the aging heart. In parallel, there is an increased deposition of collagen that will contribute to diastolic dysfunction of the heart [7].

In addition to these cardiac changes, aortic stiffness is increased and atheromatous plaques and endothelial dysfunction develop [8]. Levels of coagulation factors are elevated and those of anticoagulants are decreased, increasing the underlying incidence of thrombosis, especially above the age of 70 years [9,10].

### Physical Exercise and the Cardiovascular System

Many questions related to the effect of physical training on the health of older people still need to be answered, such as the most appropriate type and the best form of training to enhance functional gains without secondary vascular impairment. Aerobic training improves the cardiovascular system, increases muscle blood flow, arterial compliance, and endothelial function that reduce the risk of comorbidities [11]. However, the use of this exercise modality in elderly people with reduced gait speed is limited [12].

Resistance exercise is a potent tool to gain and maintain strength and skeletal muscle mass in sarcopenic older people with diminished gait speed [13,14], but high intensities (>60% of 1 repetition maximum [RM]) are required for gains in skeletal muscle mass [15]. However, older people may not be able to cope with such loads and should avoid this type of exercise as it may cause undue stress on the cardiovascular system [16].

Recently, it was reported that low-intensity resistance exercise with blood flow restriction (BFR) may be able to induce gains in strength and muscle mass in older people [17]. Typically, BFR training uses low loads (20%-30% of 1RM) and short periods of training [18], a load that is better coped with and may thus be more applicable to elderly people, especially those who are sarcopenic. However, so far there are no studies evaluating the safety of BFR training for the cardiovascular system in this population [19].

### Study Aim and Hypotheses

The aim of this study is to evaluate (1) the acute and chronic effects of resistance exercise with BFR on vascular health in elderly people with low gait speed and (2) whether low-load resistance training with BFR elicits similar gait speed and strength gains to those elicited by conventional resistance training without BFR. Specifically, we will investigate the effect of the 2 training modalities on arterial stiffness, muscle blood flow, endothelial function, gait speed, and muscle strength in this population.

Our hypotheses are that low-load resistance exercise with BFR elicits the same increase in strength and improvement in quality of life as conventional resistance training and that it has no detrimental effect on arterial stiffness, muscle blood flow, and endothelial function. The findings of this trial may inform future recommendations for training of the elderly population.

## Methods

### Study Design

This study is designed as a randomized, blind, controlled intervention trial.

### Ethical Approval

The study received ethical approval from the ethical committee of the Hospital Israelita Albert Einstein and is registered on the ClinicalTrials.gov website. Participants are only included after signing the informed consent form.

Identifiable elements, including names, phone numbers, street addresses, city or state, zip code, email addresses, and date of birth will be collected but maintained under strict confidentiality. Screening materials will be kept for the participants recruited in the study and destroyed for those that do not meet the criteria or decide not to take part. Authorization for use and disclosure of the participants’ personal health information is restricted to this specific study, and data will be kept for 5 years after publication.

### Sample Size and Power Calculation

The sample size was calculated with Stata software (StataCorp LP) for both the acute and chronic protocols based on previous reports. It has been reported that flow-mediated dilation (FMD) was on average 4.3% (SD 3.1%) and arterial stiffness was on average 9.2 m/s (SD 1.1 m/s) [20].

Power analysis indicated that we need 10 participants per group to detect a difference in FMD of 3.1% and arterial stiffness on average 1.1 m/s between groups at a statistical power of 0.80 and an alpha of .05.

Owing to the conditions and frailty of elderly people, up to 20% dropouts are expected, and therefore, we are recruiting 13 participants per group.

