### Conclusions

This trial will evaluate the effects of resistance training with or without BFR on muscle strength and gait speed and whether BFR during exercise has any detrimental or beneficial effects on arterial stiffness, muscle blood flow, and endothelial function in elderly people with low gait speed.

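### Ten per group gives about 56% power, not the stated 80%, for the planned between-group differences; ten is the answer for a one-sample or paired test

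*Protocol article*

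**What the plan says.** All the inputs stand in the Protocol article, section Sample Size and Power Calculation.

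- Variability, from an earlier report: "flow-mediated dilation (FMD) was on average 4.3% (SD 3.1%) and arterial stiffness was on average 9.2 m/s (SD 1.1 m/s").
- Target: "a difference in FMD of 3.1% and arterial stiffness on average 1.1 m/s between groups".
- Error rates: "at a statistical power of 0.80 and an alpha of .05". The section does not say whether the test is one- or two-sided. It gives no pre-post correlation, no SD of change and no covariate adjustment.
- Result: "we need 10 participants per group to detect a difference in FMD of 3.1" percentage points (and 1.1 m/s in arterial stiffness), with the 10 raised to 13 for up to 20% dropout.

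The Randomization section confirms two parallel arms of 13. FMD and arterial stiffness both appear under Primary Goals. The Conclusions section says the trial will look for "any detrimental or beneficial effects on arterial stiffness, muscle blood flow, and endothelial function".

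**The concern.** The figures printed in one short section do not fit together. A difference of one SD between two independent groups is a standard case, and ten per arm is well short of what 80% power needs. The dropout step is sound, so the shortfall lies in the base number and carries through to the 13 recruited.

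The direction of the error matters here. Under Study Aim and Hypotheses, the trial expects restricted-flow training to do no vascular harm, and the Discussion says the findings will bear on whether it is safe to prescribe. A non-significant comparison is therefore the hoped-for result. A reader told that power was 80% would take it as fair evidence against a one-SD effect. If power is really 56%, such an effect would be missed 44% of the time rather than 20%.

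**Working it through.** **Inputs** (all from Sample Size and Power Calculation, except the design, from Randomization)

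- FMD: difference 3.1, SD 3.1, so d = 3.1/3.1 = 1.0.
- Arterial stiffness: difference 1.1 m/s, SD 1.1 m/s, so d = 1.1/1.1 = 1.0.
- Alpha 0.05, power 0.80, two parallel groups, 1:1.
- Assumption: two-sided test. One-sided is also shown.

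Both outcomes have d = 1, so one calculation serves both.

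**1. Reproducing the plan's figure of 10**

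One-sample or paired t test: noncentrality = d√n, df = n − 1.

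- n = 9: noncentrality 3.00, power 0.748.
- n = 10: noncentrality 3.16, power 0.803.

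Ten is thus the smallest n that reaches 0.80 for a one-sample or paired test with d = 1. Dropout: 10/0.8 = 12.5, rounded up to 13, which matches the article.

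**2. The comparison the article describes**

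Two independent groups: noncentrality = d√(n/2), df = 2n − 2.

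| Evaluable per group | Noncentrality | Power, two-sided | Power, one-sided |
|---|---|---|---|
| 10 | 2.24 | 0.562 | 0.694 |
| 13 | 2.55 | 0.687 | 0.797 |
| 16 | 2.83 | 0.781 | 0.868 |
| 17 | 2.92 | 0.807 | 0.886 |

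The normal approximation agrees: n = 2(1.960 + 0.842)²/d² = 15.7, so 16 per group, and power at n = 10 is 0.61 two-sided or 0.72 one-sided. By the t test, 80% power needs 17 evaluable per group two-sided, or 14 one-sided. With the article's dropout allowance, 17/0.8 = 21.25, so 22 recruited per group.

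**3. Differences detectable with 80% power (two-sided t)**

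- n = 10: d = 1.325. FMD 1.325 × 3.1 = 4.1 points; stiffness 1.325 × 1.1 = 1.46 m/s.
- n = 13: d = 1.145. FMD 1.145 × 3.1 = 3.55 points; stiffness 1.145 × 1.1 = 1.26 m/s.

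**4. Can the pre-training measurement close the gap?**

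Let r be the pre-post correlation, which the article does not give. A change score multiplies the SD by √(2(1 − r)); ANCOVA multiplies it by √(1 − r²) and uses df = 2n − 3.

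| n per group | r | Change score | ANCOVA |
|---|---|---|---|
| 10 | 0.5 | 0.56 | 0.68 |
| 10 | 0.66 | – | 0.80 |
| 10 | 0.7 | 0.78 | 0.84 |
| 13 | 0.49 | – | 0.80 |

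At 10 per group the change score reaches 0.80 only at r of about 0.72.

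**The case against.** The strongest reply is that the article condenses a fuller calculation. Measurements are taken before and after training, so a two-group calculation adjusted for the pre-training value could also return 10 per arm, with r of about 0.66 (ANCOVA) or 0.72 (change score). The software command is not shown, so the paired-test explanation is only an inference. This part stands: the exact match at n = 10 suggests how the number arose but does not prove it. It does not clear the section, which prints SDs beside outcome means, gives no correlation, and attributes 80% power to those inputs. If the printed SDs were really SDs of change, the difference would still be one SD and the power still 0.56.

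A second reply is that the hypothesis of no detrimental effect is directional, so a one-sided test could be meant. The two-sided reading is indeed an assumption, though it is the usual default and fits the stated interest in harm or benefit. One-sided power at 10 per arm is 0.69, still short of 0.80.

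A third reply is that the choice of analysis model belongs in a SAP that is not shown. That is fair, and the absence of a model is not the complaint. The complaint is that the printed sample size, difference, SD, alpha and power disagree.

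**Conclusion.** The power statement is wrong as written. On the article's own inputs, 10 evaluable participants per arm give 0.56 power for a one-SD between-group difference with a two-sided t test at 0.05, and 13 give 0.69. A one-sided test gives 0.69 and 0.80, the latter only if nobody drops out. No unadjusted two-sample version of the calculation gives 80% at 10 per arm; a two-sided test needs 17. The conclusion assumes equal SDs, independent arms and the printed SDs as the relevant ones. Only an unstated pre-post correlation of about 0.66 or more would make 10 per arm sufficient. That a paired or one-sample formula was used remains a probable explanation, and the finding does not depend on it.

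This must be corrected, because the stated power would otherwise support reading a null result on FMD or pulse wave velocity as evidence of vascular safety.

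**What to change.** 1. Replace the power statement with, for example: 'For a between-group difference of one SD (3.1 points of FMD; 1.1 m/s in pulse wave velocity), two-sided alpha 0.05 and an unadjusted t test, 10 evaluable participants per arm give power of about 0.56, and 13 per arm about 0.69. With 80% power the detectable differences are 4.1 points and 1.46 m/s at 10 per arm, or 3.55 points and 1.26 m/s at 13 per arm.'
2. State that the test is two-sided.
3. Make the primary between-group comparison an ANCOVA of the post-training value on group and pre-training value. State the assumed pre-post correlation, with its source, for each outcome. Power reaches 0.80 at 10 per arm if r is at least about 0.66, and at 13 per arm if r is at least about 0.49. If r is nearer 0.5 with 10 per arm, state power of about 0.68.
4. Report the between-group difference with its 95% confidence interval, and do not present a non-significant result as showing no vascular effect. Neither the corrected power nor ANCOVA would by itself make a null result evidence of no harm.

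The cost is wording in the protocol and SAP and a less favourable power figure. ANCOVA uses measurements already planned. More participants are not needed if the correlation condition is met or the lower power is openly accepted. Keeping 80% power without adjustment would need 17 evaluable, or about 22 recruited, per arm.

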### Eligibility

The eligibility criteria for participation in the study are provided in Textbox 1.

Inclusion and exclusion criteria.Inclusion criteria:Elderly people aged ≥65 yearsGait speed <0.9 m/sExclusion criteria:Smoking <6 monthsPrevious deep venous thrombosisUncontrolled arterial hypertension (blood pressure >160/100 mm Hg)Uncontrolled dyslipidemia (total cholesterol >220 mg/dL)Infections within the past 1 monthOsteoarticular or neurological problems that prevent trainingUse of oral anticoagulantsSymptomatic peripheral obstructive arterial disease or ankle-brachial index <0.9History of anemia, cerebrovascular disease, or myocardial infarction in the last 6 monthsElderly people with uncontrolled diabetes mellitus or peripheral neuropathyUse of double antiplatelet agents: aspirin, Aggrenox, cilostazol, eptifibatide, ticlopidine, and tirofiban

### Participant Information and Informed Consent

Eligible participants are recruited primarily based on the results of a gait speed test. They consult with a cardiologist and a physiatrist to assess their health and determine whether they can participate in the study. In addition, medical records of the participants will be filled in for later analysis. Eligible participants are informed of their rights, and the procedures of the study and will be allowed to participate only if they provide written informed consent. Relatives are informed about the details of the tests and exercise sessions, if necessary.

### Recruitment

Participants are recruited from the Vila Mariana Unit of the Hospital Israelita Albert Einstein and elderly care centers in São Paulo.

### Randomization

Using a website [21], participants are randomized into two groups, each with 13 participants:

Low-load resistance exercise group (20% of 1RM) with BFR (resistance exercise with blood flow moderation, KAATSU);Conventional resistance exercise (CRE) group (60% of 1RM).

The block sizes and randomized sequences are hidden from those who recruit or allocate participants to prevent predictability of the next assignment [22]. The participants must be aged 65 years or above.

### Blinding

Research team members administering clinical assessments are blinded from participant allocation. Participant allocation will not be revealed during the study.

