### Primary Goals

#### Venous Occlusion Plethysmography Protocol

Muscle blood flow is evaluated with venous occlusion plethysmography. The participant’s legs are elevated above the level of the heart to ensure adequate venous drainage. A mercury-filled silastic tube, connected to a low-pressure transducer and a plethysmograph (DE Hokanson), is placed around the largest circumference of the calf region. One cuff is placed around the ankle and another around the thigh. The ankle cuff is inflated to a suprasystolic pressure, 30 seconds before starting the measurements. At 15-second intervals, the cuff around the thigh is inflated above the venous pressure for a period of 7 to 8 seconds. Increased tension in the silastic tube reflects an increase in leg volume and vasodilation. The signal of the muscle blood flow wave is recorded on a polygraph and analyzed every minute, averaging 3 records per minute. The protocol is performed in a cycle of 5 min of rest, 3 min of isometric exercise, and 2 min of recovery [25].

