#### One Repetition Maximum Test (Knee Extension and Seated Leg Press)

The dynamic force of the lower limb muscles is evaluated by the maximal repetition of knee extension and leg press exercise, according to the protocol presented in a previous study [32]. The partipants perform a warm-up comprising 1 series with 10 unloaded repetitions. After this step, the mass to be lifted is progressively increased until the maximum load that can be lifted is reached, with a maximum limit of 5 attempts and a 3 min to 5 min interval between them. The test is conducted by a physical education professional who verbally encourages the participants throughout these steps and performs the load adjustment at weeks 5 and 10.

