### Adverse Events and Risks

BFR exercise may cause headache, red spots, redness, pain, and discomfort in lower limbs during or after exercise sessions.

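### The general assessor-blinding statement is contradicted for the 1RM strength outcome, because the role that runs and coaches the test also sets the arm-specific training load

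*Protocol article*

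**What the plan says.** The Study Design section calls the study a "randomized, blind, controlled intervention trial". The Blinding section specifies this in two sentences: "Research team members administering clinical assessments are blinded from participant allocation", and "Participant allocation will not be revealed during the study". Neither names the outcomes covered, and neither exempts any outcome or any member of staff.

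The 1RM section describes the procedure as one "conducted by a physical education professional who verbally encourages the participants throughout these steps and performs the load adjustment at weeks 5 and 10". The arms differ in load: the Randomization section defines one as "Low-load resistance exercise group (20% of 1RM) with BFR" and the other as conventional exercise at 60% of 1RM. Table 2 carries these percentages through the 12-week programme.

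The abstract lists strength as a secondary outcome. The Study Aim and Hypotheses section asks whether the low-load arm gains strength as the conventional arm does, and hypothesises that the gain is the same.

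**The concern.** A 1RM result depends on how hard the participant tries, and here the tester encourages the participant aloud. Blinding the tester is the main protection against uneven encouragement. If the tester knows the arm, more or less urging in one arm moves the measured difference directly.

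The hypothesis makes this more serious. The trial hopes to conclude that the arms gain equally, so extra encouragement in the KAATSU arm could mask a real deficit and push toward the expected answer. Bias in the other direction could produce a difference that does not exist. With 13 participants per arm, or 10 after the planned dropout, there is little data with which to detect or correct either.

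A second and weaker issue concerns plethysmography in the acute study. The assessor works on the legs 60 minutes after a session that, in the KAATSU arm, may leave visible marks.

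**Working it through.** The plan states no figure on this point, so the check sets the sections side by side.

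**Step 1: what the blinding statement covers.** The Blinding section covers staff who administer clinical assessments. The term is not defined and no outcome is excluded. On its plain reading it includes the 1RM test, which is how the trial measures strength.

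**Step 2: who runs the 1RM test.** A physical education professional conducts it, encourages the participant and adjusts the load (1RM section). One role does all three.

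**Step 3: what load adjustment requires.** Training load = 1RM × 0.20 (KAATSU) or 1RM × 0.60 (conventional). From the same 1RM the two loads differ by a factor of 0.60 / 0.20 = 3. The calculation cannot be done without knowing the arm.

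**Step 4: when the role learns the arm.** The Chronic Protocol section and Table 2 place load adjustment at sessions 9 and 18. At 2 sessions per week, session 9 falls in week 5 (9 / 2 = 4.5) and session 18 in week 9 (18 / 2 = 9). Both come before the post-training measurement, so the role is unblinded by week 5 at the latest. The 1RM section gives weeks 5 and 10, and its second date does not match session 18. The two sections should be reconciled, but either date precedes the final test.

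**Step 5: result for 1RM.** Steps 1 to 4 cannot all hold together with blinded 1RM assessment. The second blinding sentence also cannot hold for the staff who set loads.

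**Step 6: the other outcomes.**

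| Outcome | What the protocol article says | Conflict with the blinding statement |
|---|---|---|
| 1RM strength | Tester also adjusts the load | Yes |
| Flow-mediated dilation | Measured at the brachial artery | None shown |
| Pulse wave velocity | Carotid-femoral tonometry | None shown |
| Gait speed | Timed walk; no link to the trainer stated | None shown |
| Plethysmography | "One cuff is placed around the ankle and another around the thigh" | Possible risk only |

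The plethysmography entry combines three statements. Restriction exercise may cause "red spots, redness, pain, and discomfort in lower limbs during or after exercise sessions" (Adverse Events and Risks). The device is placed on the leg (Venous Occlusion Plethysmography Protocol). In the acute study it is used 60 minutes after exercise (Acute Protocol). No section says that marks last 60 minutes or that the assessor sees them.

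**Step 7: scale, as an illustration only.** Assume that encouragement shifts one arm by b standard deviations. A true deficit of b SD would then appear, on average, as no difference. For a two-sided 5% t test with no true difference and n per arm, the noncentrality is b × √(n/2) on 2n − 2 degrees of freedom:

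| Assumed b | n per arm | Noncentrality | Rejection probability |
|---|---|---|---|
| 0.25 | 10 | 0.559 | 8.3% |
| 0.25 | 13 | 0.637 | 9.4% |
| 0.50 | 10 | 1.118 | 18.5% |
| 0.50 | 13 | 1.275 | 23.2% |

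The values of b are assumptions with no source in the protocol article. The table also describes a test for a difference, whereas the stated hypothesis is equal gain. It shows how sensitive a trial of this size is to such a shift. It does not estimate the bias in this trial.

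**The case against.** The strongest reply is that clinical assessments is an undefined term. The Acute Protocol section speaks of clinical tests where it asks participants to avoid caffeine, chocolate and tea, and it may mean the vascular tests. If 1RM is outside the term, the first blinding sentence and the 1RM section are compatible and only clarification is needed. The 1RM section also names a role, which need not be one individual, and it ties that role to the load adjustments without saying who runs the before and after outcome tests.

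Part of this stands. That one individual does everything is an inference, though the text describes a single 1RM procedure with a single role and mentions no separate tester. The narrow reading of the term does not rescue the second blinding sentence, which cannot be true of staff who set loads. It would also leave the strength outcome outside any claim of blinding, and the protocol article nowhere says so.

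A reader might infer that assessor blinding fails across the trial. The documents do not support that. Nothing contradicts blinding for flow-mediated dilation, pulse wave velocity or gait speed, and the restriction cuffs are applied by an instructor who is not identified as an outcome assessor. A reader might also treat skin marks as a proven route of unblinding, but the text gives only a possibility, with no frequency, duration or visibility. Finally, the label blind might be read as a claim that participants are masked. The Blinding section never says this, and participants could not be masked to cuffs or to a threefold difference in load.

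**Conclusion.** The blinding statement is contradicted for one outcome, 1RM strength. That outcome is secondary but carries half of aim 2 and an explicit hypothesis of equal gain, so the defect bears on a named conclusion of the trial. The direction and size of any bias are unknown.

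The conclusion rests on two readings: that the 1RM test counts as a clinical assessment, and that the role described in the 1RM section also runs the post-training test. Both are the natural reading of the text, but neither is stated outright. For plethysmography after the acute session, unblinding is a possible risk and not a shown failure. The point is a worthwhile, cheap correction and does not undermine the vascular outcomes.

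**What to change.** 1. Have the before and after outcome 1RM tests run by existing staff who neither train participants nor set loads, using scripted encouragement. Pass only the 1RM value to the trainer, who computes the load.
2. If that is not feasible, declare 1RM unblinded and limit the strength conclusion accordingly.
3. Describe the trial as assessor-blinded for named outcomes, with participants and trainers open-label, and reword the sentence on not revealing allocation to match.
4. As a low-cost safeguard, read the plethysmography tracings under the identification number already described in Data Management, with arm and visit labels removed. This protects the reading but not the recording itself.
5. Reconcile the timing of the second load adjustment between the 1RM section and Table 2.

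The cost is a small scheduling burden for the 1RM tests and some file coding. Items 1 to 4 leave sample size, visits and training content unchanged.
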